**Fig 1 pone.0258134.g001:**
[figure not shown]
Flow diagram of selection and fieldwork at village/district level (3 districts per country).

### Research aim

To investigate the potential health impacts of pesticides use on agricultural workers’ health.

### Outcomes

a. Acetyl cholinesterase concentrationsb. Self-reported ill-health measures separately and together

### Predictors

2. Practices/Behaviours
Likely to increase exposureLikely to decrease exposure3. Knowledge

### Covariates

Location:country, district, type of area, farm type, cropPersonal characteristicsAge, gender, income, socio-economic status (SES), migration status, employment status, education, ability to read and write, distance between home and farm, hours worked.

### Analysis outline

Data will be summarised using appropriate descriptive statistics; we will report on associations between agricultural methods, health knowledge, health-protective practices, self-reported illness and blood test results.

Data from each country will be analysed separately before considering whether an analysis of pooled data is appropriate.

Description of all variables: frequencies, or ranges and measures of central tendencyCombining structured interview responses to give overall measures of: outcomes, knowledge, practices/behaviours and exposures. The variables to be combined will be listed *a priori*.Measures of ill-health, knowledge, behaviours and exposures will be described separately and together.Bivariate explorations will be used to examine the variables shown in Table 1.

**Table 1 pone.0258134.t001:** Contingency tables for each comparison.

	Ill-health measures	Exposure	Practices/behaviours	Knowledge	Cholinesterase concentration
Ill-health measures					
Exposure					
Practices/behaviour					
Knowledge					
Cholinesterase concentration					

4. Multivariate analysesPrimary outcomes: AChE concentrations, ill-health measures, separately & togetherCovariates to be tested one by oneCovariates with P<0.20 will be entered into exploratory models

a) Logistic regression: high AChE concentration, any ill-health, each health issue (modelling strategy to be based on backwards LR, -2LL, VIF, check enter model)

Predictors:

1. Behaviours
a. Likely to increase exposureb. Likely to decrease exposure2. Knowledge score3. Cholinesterase concentrations (when exploring ill-health)4. Significant covariates from one-by-one testing will include: location, SES, education, literacy (ability to write), age, gender, hours worked, distance between home and farm.

Sensitivity analyses will, in turn, exclude:

Migrant workersEarlier diagnosis of pesticide poisoning

A priori sub-group analyses:

Each countrySelf-employedLowest SES or income categoryNo formal education

b) Meta-analysis of all countries. A random-effects meta-analysis approach incorporates an assumption that the different studies are estimating different, yet related, intervention effects. It is assumed that there is a similarity in the patterns found in, for example, a study of pesticides impacts in three countries, but that the effects found will not be identical due to contextual factors. [65]. The approach provides a way to estimate how far differences reflect true effects in data from multiple countries, rather than chance differences arising from sampling, Meta-analysis of continuous variables with data that are not normally distributed will not be undertaken. We anticipate equal numbers of responses from each country, reducing the effects of study weighting by size. If heterogeneity of country findings is moderate or low, we shall consider multilevel modelling of pooled data to account for country in addition to location, and farm and crop type. Heterogeneity will be assessed according to the GRADE guidelines, including: variation in estimates across the different countries, particularly where confidence intervals do not overlap, and the *I*^*2*^ test of heterogeneity. We shall take 50–90% as substantial, and 75–100% *I*^*2*^ values as considerable heterogeneity [66]. Any *I*^*2*^ values over 90% will jeopardise the value and reporting of a meta-analysis.

*A posteriori* subgroup analyses will be used to explore links for future studies, rather than study outcomes. It is difficult to speculate on the nature of such analyses, but they might include exploration of the data by respondents’ ages or gender.

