#### Sampling frame

Background inquiries in Thailand suggest that numbers of households engaged in vegetable farming in districts (villages) in the study province growing these crops for the commercial market do not exceed 200 per district. Our resources will allow us to interview 120 individuals per district (representing about 60% of households in that district), and hence obtain 360 responses from 3 districts in each country.

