#### Clustering

We will interview only one person from any one household to avoid data replications on household-level behaviours, such as laundry; this also allows us to use a single intra-cluster correlation coefficient (ICC) for responses from the same district. With no ICC available from our single-district Thai pilot study, we have used the unadjusted median ICC observed in primary care studies across a range of variables: (interquartile range [IQR] 0 to 0.032) [61], and set the ICC here to 0.01. With m = 120 interviews per district, our design effect, calculated as 1+(m-1)*ICC [62] is 2.19; this compares with design effects values ~1.5, as reported in surveys of developing countries [63]. Our confidence intervals are thus inflated by a multiplicative factor of 1.48 over those based on the assumption of independent responses; this adjustment accounts only for clustering within districts (groups of villages).

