#### Precision

We are testing the prevalence of cholinesterase concentrations likely to impact on health, estimated at 35% [59,60]. We are able to recruit 360 respondents in each country. We calculate that 360 respondents will allow us to verify this 35% prevalence, with 95% confidence intervals lying between 28% and 42%.

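### Backward-eliminated maximum-likelihood models for each health issue in each country, whatever the number of cases, risk non-finite or exaggerated odds ratios for issues reported by about 5% of workers or fewer

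*Protocol article*

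**What the plan says.** In the Protocol article, item 4a of the Analysis outline lists the outcomes to be modelled as "Logistic regression: high AChE concentration, any ill-health, each health issue". It gives one strategy for all of them: "modelling strategy to be based on backwards LR, -2LL, VIF, check enter model". Covariates are tested one at a time, and those with P<0.20 go into models that the article calls exploratory. The predictors of ill-health are two groups of behaviours (raising and lowering exposure), a knowledge score and cholinesterase. The named covariates are location, SES, education, literacy, age, gender, hours worked and distance from home to farm.

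The unit of analysis is the country: "Data from each country will be analysed separately before considering whether an analysis of pooled data is appropriate". The Sampling frame section expects to "hence obtain 360 responses from 3 districts in each country". The same item 4 names AChE and the ill-health measures, singly and combined, as primary outcomes.

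The article gives no expected prevalence for any symptom. Its sample size rests only on the precision of the AChE prevalence.

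**The concern.** Likelihood-ratio elimination and -2 log likelihood imply ordinary maximum likelihood, and no penalised or exact method is named. The rule is unconditional: an issue reported by 10 workers is modelled in the same way as one reported by 120. With few cases and many candidate terms, two things can go wrong. A covariate pattern may separate cases from non-cases, so that an odds ratio has no finite estimate. And terms that survive elimination tend to do so because their estimate happens to be large.

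At stake are the symptom-specific odds ratios. They belong to the stated primary outcomes, and the Reporting section says the models will show which behaviours could be targeted.

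**Working it through.** **1. The plan's own figure.** The Clustering section says "With m = 120 interviews per district, our design effect, calculated as 1+(m-1)*ICC [62] is 2.19": 1 + 119 × 0.01 = 2.19, with square root 1.48. For 35% of 360, the standard error is √(0.35 × 0.65 / 360) = 0.0251. Then 1.96 × 0.0251 × 1.48 = 0.073, giving 27.7% to 42.3%. This agrees with the Precision section ("360 respondents will allow us to verify this 35% prevalence, with 95% confidence intervals lying between 28% and 42" per cent). The sample size is sound for its purpose, but that purpose is an outcome with 0.35 × 360 = 126 cases.

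**2. Candidate parameters in an ill-health model.**
- Main predictors: two behaviour groups, knowledge and cholinesterase = 4.
- Covariates: location (three districts) 2, and SES, education, literacy, age, gender, hours and distance 1 each = 9.
- Total 4 + 9 = 13. This is a minimum: it rises if SES, education or cholinesterase has more than two categories. The AChE model has 12, since cholinesterase does not predict itself.

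**3. Simulation of the stated procedure.** The setting was one country with 360 workers in three districts and 13 candidate parameters.
- Assumed covariates: cholinesterase binary at 35%; SES, education, literacy and gender binary at 25%, 15%, 12% and 45%; the remaining non-district terms standard normal.
- Assumed true effects: log odds ratio 0.4 and −0.4 for the two behaviour scores; odds ratio 2.0 for cholinesterase, 1.5 for education and 2.0 for literacy; none for the rest.
- Procedure: P<0.20 screen on covariates, then backward likelihood-ratio elimination. The removal level of 0.10 is assumed, because the article gives none.
- Non-finite means non-convergence, any |log odds ratio| above 10, or no cases.
- Runs per prevalence: 1,000 for the full model and 250 for screen plus elimination.

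Cases are 360 × prevalence. Every prevalence is an assumption.

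| Prevalence | Cases | Cases / 13 | Non-finite, all 13 terms | Non-finite, after screen and elimination | Median retained cholinesterase OR (true 2.0) | Ratio to truth | Runs retaining it |
|---|---|---|---|---|---|---|---|
| 1% | 3.6 | 0.28 | 86% | 48% | 7.0 | 3.5 | 8% |
| 2% | 7.2 | 0.55 | 55% | 31% | 5.3 | 2.6 | 17% |
| 3% | 10.8 | 0.83 | 28% | 22% | 4.0 | 2.0 | 22% |
| 5% | 18 | 1.4 | 6.5% | 5.6% | 3.2 | 1.6 | 39% |
| 10% | 36 | 2.8 | 0.2% | 0% | 2.5 | 1.25 | 60% |
| 20% | 72 | 5.5 | 0% | 0% | 2.2 | 1.1 | 80% |
| 35% | 126 | 9.7 | 0% | 0% | 2.1 | 1.05 | 86% |

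Monte Carlo standard error at 22% is √(0.22 × 0.78 / 250) = 2.6 points. At 3% prevalence the retained median rests on about 0.224 × 250 = 56 fits.

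**4. A second simulation** used the same screen, elimination and 0.10 level with a true odds ratio of 1.5. It gave non-finite fits in about 20% of runs at 3%, 6% at 5% and under 1% at 10%. Median retained odds ratios were 3.7, 2.8, 2.3 and 1.9 at 3, 5, 10 and 20%. Divided by 1.5, these are 2.5, 1.9, 1.5 and 1.3 times the truth.

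**5. Where the exaggeration comes from.** In the full model without selection, the mean cholinesterase log odds ratio among finite fits was 1.09 times the truth at 3% and 1.06 times at 5%. For the first behaviour score it was 1.21 and 1.11 times. When that score survived elimination, its mean log odds ratio was 1.80 and 1.53 times the truth. Selection therefore adds most of the excess.

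**6. Penalised likelihood.** Firth estimation of all 13 terms without selection (300 runs per prevalence) was always finite. Mean log odds ratios relative to the truth were 0.93 to 1.07 at 2%, 0.93 to 0.97 at 3%, 0.95 to 1.09 at 5% and 1.00 to 1.06 at 10%. At 1% (3.6 cases) they were 0.66 to 1.10, which is finite but not reliable.

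**7. Across countries.** If prevalence is equal and countries are independent, the chance that at least one of the three final models contains a non-finite estimate is 1 − 0.78³ = 53% at 3% and 1 − 0.944³ = 16% at 5%. The affected term need not be the one carried into the meta-analysis.

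**The case against.** The strongest objection is that everything turns on a number the article does not give. Participants must have applied pesticides within three weeks, so symptoms may be common, and at 20% or more the plan works acceptably. This stands, and it makes the point conditional. A reader might infer that symptom odds ratios will be infinite or several times too large; the documents do not support that.

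The P<0.20 screen means the 13-term model is not the final one. That also stands: at 2% prevalence non-finite fits fall from 55% to 31%. Failure rates for the full model therefore overstate what the planned procedure would do, and they vary with the assumed covariates. The screen does not remove the problem, and selection causes most of the exaggeration.

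The models are called exploratory, which softens the consequence. But the ill-health measures are also primary outcomes, and the results are meant to identify behaviours to target. It is not shown that policy would be pointed at the wrong behaviours: enlarging a true association is not the same as inventing one.

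A minimum case count could sit in an analysis plan that is not shown, and the section on measuring cholinesterase refers to specialist advice on multivariate analysis. The absence of such a rule is therefore not held against the article. The point concerns the method it does fix, without condition.

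A reader might also infer that a rule of ten cases per parameter is needed, or that the countries must be pooled. Neither follows. Ten times 13 is 130 cases, or 36% of 360, which would shut out even a 35% outcome with 126 cases. Mandatory pooling would conflict with separate national reporting and with pooling that depends on heterogeneity.

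**Conclusion.** The concern holds, conditional on prevalence, and should be addressed. For any health issue reported by about 5% or fewer of a country's 360 workers (18 cases or fewer), the stated procedure risks non-finite odds ratios: roughly 20% of final fits at 3% and 6% at 5%, against under 1% at 10%. Odds ratios that survive elimination are exaggerated by about 1.6 to 2.5 times at 3 to 5% and 1.25 to 1.5 times at 10%. At 20% the excess is about 1.1 to 1.3 times. The AChE model, at the expected 35%, is not in question.

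These sizes rest on assumed prevalences, covariate distributions, true odds ratios and a 0.10 removal level, and on district entering only as fixed terms. The two simulations agree closely on non-finite fits and in direction on exaggeration, but the exact figures should not be read as predictions for this study.

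**What to change.** For each single health issue, replace backward elimination in item 4a with a country model fitted by Firth-penalised logistic regression, with profile penalised-likelihood intervals. Use a prespecified set of terms: the behaviour groups, knowledge, cholinesterase, district and a few named covariates. Firth estimation deals with the non-finite estimates, and dropping elimination deals with most of the exaggeration.

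Where a country has very few cases of an issue, for example fewer than about 10, report frequencies only. The exact cut-off is a judgement. In the simulation, penalised estimates were still close to the truth on average at about 7 cases and unreliable at about 4.

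Leave the country-first reporting and the conditional pooling or meta-analysis as they are.

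The cost is a change of wording, a standard routine and slightly more analysis work, with no new data. The price is that the rarest issues will have no adjusted country-level odds ratio.

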Most pesticides are synthetically-produced organic and inorganic chemical compounds, although biological agents are also coming into wider use [25]. The most commonly imported pesticides are organophosphates (OPPs) and carbamates [26]. OPPs and carbamates kill insects by blocking acetylcholinesterase (AChE), an enzyme that catalyses hydrolysis of a neurotransmitter acetylcholine, resulting in overstimulation of the neuromuscular system and the parasympathetic nervous system. Exposure to OPPs by inhalation or ingestion with or without food is toxic to the human body. It can be detected by a reduced AChE concentration in capillary blood. Acute OPP poisoning symptoms include: increased salivation, diarrhoea, vomiting, muscle tremors, gastrointestinal upset, and confusion [27]. The onset of symptoms can start within minutes or hours and last for days to weeks. In the long term, lower-dose exposure to OPPs has been reported to cause polyneuropathy and cardiovascular diseases [28]. Carbamates can also pose both health and environmental hazard, including through groundwater contamination [29] and food [29,30].

The health impact of pesticide use has been a topic of heated debate for many years in Asian countries, both at national and local government levels. There is a need to prevent adverse health effects as part of a wider pesticides management strategy, and there would be major advantages in establishing a framework for cooperation within the Association of Southeast Asian Nations (ASEAN). At present, countries in the Mekong region have only their differing national strategies, and it would be valuable to compare approaches and develop a more uniform approach that takes the best ideas from each country.

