### Structured interviews

A researcher-administered structured interview will be used to collect data concerning the nature of agricultural work, pesticides use, workers’ health knowledge, health protective practices, and self-reported experiences of ill health. Interviews of this type are sometimes described as survey interviews or standard interviews, and contain mainly closed-end questions that resemble a questionnaire, but are typically read to the respondent and completed by the researcher. Research assistants (paid research staff or postgraduate students) will be trained to explain the meaning of the various items to workers and complete the form in their presence. The structured interview is adapted from the instrument used in a study by [name] and associates [1]. Content validity of items in that instrument were confirmed by an index of conjugate (IOC) calculation. All items had IOC scores greater than 0.5 and an internal reliability coefficient (Cronbach’s α) of more than 0.7. The original Thai interview containing 59 items has been expanded to 83 items in the instrument prepared for the present study. This was modified *inter alia* to use terms and units that apply to all ASEAN countries, to ensure that multi-choice items covered all logical possibilities, and to add additional questions regarding specific pesticides types (insecticides, herbicides and fungicides), crop types, planting periods, self-medication and medicines prescribed by healthcare professionals.

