As a first step health or local government personnel familiar with the district will compile a list of workers involved in vegetable production in the village/district. The list will include all members of households aged 18 and above who work regularly as farmers. Candidates may be natives or migrant workers, but must be fluent in the main language of the study country. They will be encouraged to participate through the offer of a small reward, a cash payment of less than £1 GBP payable on completion of the study. The list will comprise information on name, large or small farm and gender. The number of households and people on the list will be noted.The research team will use a randomising procedure to select from the list 120 first choice workers’ households and 30 reserves (with the latter listed in order).The health or local government staff assisting with the project will be advised of the selection. They will approach the first 120 named candidate households selected by the research team as first choices for inclusion to ask whether a volunteer adult household member is willing to meet with the research team to discuss participation in a research project on pesticides use. Information sheets will be distributed.Those volunteering will be contacted by researchers. The content of the information sheet will be explained and opportunities to ask questions provided. Those indicating their consent to participate will be screened to determine whether they meet the study inclusion criteria (which include a check that only one member per household takes part). Those selected will sign or provide a thumb print on a consent form.The main interview will be conducted either immediately or within a few daysWhen interviews are completed, consent to take blood samples will be confirmed. Only participants who agree to both interview and blood sample will be included in the study. Capillary blood samples will be taken using finger-prick lancets. In Thailand local public health staff measure AChE levels of farm workers routinely as part of a government health promotion initiative, using test kits identical to those purchased from the Thai GPO for the study. If tests were completed within the past 4 weeks these results will be used for this study, as was the case in the pilot study. If no such data are available for consenting participants from the local health service, finger-prick blood tests will be undertaken after the interviews.In the event that candidates from the original 120 selections fail to meet the research team, are found to be ineligible or do not consent to participate in all stages of the study, additional candidates from the reserve list will be approached one by one to make up the numbers.Participants completing the interviews will be given a health protection information sheet detailing dos and don’ts of safe pesticides use.Participants completing the blood tests will be advised of where to seek help if any adverse effects (such as infection) arise. They will also be told how they will be notified of the blood test result and that local health staff will advise them on necessary treatment or behavioural change. They will be given the small study reward.

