
Agricultural workers eligible for inclusion in the study must:

be involved in cultivating vegetables as a main crop for commercial sale for at least 10 months a year (fruit may be included as a secondary crop);have applied pesticides to crops in the last 3 weeks.be aged 18 or above

Workers will be excluded if they:

work mainly with organic vegetables or fruits;cultivate hydroponics;cannot communicate in the primary native language of the study country;are from the same household as an already-recruited participant.

We have added the requirement that workers should have used pesticides in the last three weeks because it is known that, following exposure to organophosphates, AChE levels begin to rise to near-normal levels after that period [64].

A flow diagram illustrating the fieldwork process is shown in Fig 1.

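### One AChE reading covering roughly three weeks is set against all self-reported ill-health, and nothing shown ties the illness outcome to that window

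*Protocol article*

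**What the plan says.** - **Outcomes and predictor.** Analysis outline, item 4a, names the logistic outcomes as "high AChE concentration, any ill-health, each health issue". For the ill-health models its predictor list includes "Cholinesterase concentrations (when exploring ill-health". Ill-health measures stand among the primary outcomes, taken separately and together. (The adverse AChE category is the low one, below 75. The word high in the quote is a separate wording matter.)
- **What AChE reflects.** The eligibility criteria in Fieldwork process require that workers "have applied pesticides to crops in the last 3 weeks". The reason given is that, after organophosphate exposure, "AChE levels begin to rise to near-normal levels after that period".
- **What illness covers.** Background says of acute poisoning: "The onset of symptoms can start within minutes or hours and last for days to weeks". It adds: "In the long term, lower-dose exposure to OPPs has been reported to cause polyneuropathy and cardiovascular diseases".
- **How illness is measured.** Structured interviews describes the data as "self-reported experiences of ill health". The article gives no recall period or onset rule, and the 83-item form is not shown.
- **When blood is tested.** Testing normally follows the interview. For routine Thai tests, Fieldwork process says: "If tests were completed within the past 4 weeks these results will be used for this study".
- **Handling of past illness.** One sensitivity analysis drops workers with a previous poisoning diagnosis.

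**The concern.** The protocol uses the three-week window to choose who is eligible, so exposure and AChE are aligned by design. The illness side of the comparison, as described, is not. One reading of recent exposure is set against every health issue and against an all-inclusive composite, although the protocol's own account separates illness that fits the window from illness that builds up over years.

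The fourth objective includes the association between reported ill-health and AChE, and the Introduction presents the pairing of blood tests with self-report as a strength of the design. If the illness outcome mixes recent symptoms with earlier or chronic illness, a weak, null or even inverse association is hard to interpret. It could mean little effect, or only that the two measures refer to different periods.

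**Working it through.** **1. The time frames side by side**

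| Element | Period in the article |
|---|---|
| AChE reading | recovery begins about 3 weeks after exposure |
| Qualifying pesticide use | last 3 weeks |
| Acute symptoms | onset in minutes or hours, lasting days to weeks |
| Polyneuropathy, cardiovascular disease | long-term, lower-dose exposure |
| Illness outcomes in the models | no period given |
| Existing Thai AChE result | up to 4 weeks old |

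The first three rows fit together. The last three do not clearly fit with them.

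**2. The plan's own figure.** The sample size rests on prevalence (Sample size basis, Clustering, Precision). Design effect = 1 + (120 − 1) × 0.01 = 2.19, and √2.19 = 1.48. The 95% interval is 0.35 ± 1.96 × √(0.35 × 0.65 / 360 × 2.19) = 0.35 ± 0.073, or 27.7% to 42.3%. This matches the stated 28% to 42%. The present point does not touch it. No power is stated for the AChE-illness association.

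**3. Size of the possible bias (illustration).** The article gives no illness rates, so these inputs are assumed: recent illness in 15% of workers without low AChE, and a true odds ratio (OR) of 2.0 for recent illness.

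- Recent illness with low AChE: odds 0.15/0.85 × 2 = 0.353, so 0.353/1.353 = 26.1%.
- Composite in each AChE group: P(any) = 1 − (1 − recent)(1 − earlier), taking recent and earlier illness as independent within the group.
- Example with 40% earlier illness in both groups: 1 − 0.85 × 0.60 = 0.490 and 1 − 0.739 × 0.60 = 0.557. OR = (0.557/0.443)/(0.490/0.510) = 1.31.

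Composite OR by prevalence of earlier illness among workers without low AChE:

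| Link of earlier illness to current low AChE | 10% | 20% | 40% |
|---|---|---|---|
| None (OR 1.0) | 1.64 | 1.47 | 1.31 |
| Habitual exposure (OR 2.0) | 2.13 | 2.19 | 2.24 |
| Ill workers now spray less (OR 0.5) | 1.39 | 1.11 | 0.84 |

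With recent illness at 10% or 25% instead of 15%, the no-link row becomes 1.53/1.36/1.22 or 1.77/1.63/1.45. The spray-less row becomes 1.24/0.96/0.74 or 1.58/1.31/1.00.

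**4. Power in the no-link case.** Inputs: 360 per country, 35% with low AChE (126 against 234), two-sided 5%, normal approximation for two proportions. Power is 72% with no earlier illness, and 53%, 39% and 22% with 10%, 20% and 40%. Dividing the sample by 2.19 gives 41%, then 28%, 21% and 12%. That factor was derived for a prevalence and need not apply in full to a comparison made within districts, so these lower figures are indicative.

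**5. Existing Thai tests.** Count days back from the interview, and take eligibility and test age from the same day. Qualifying spraying lies in days 0 to 21. A test *d* days old reflects roughly days *d* to *d* + 21. The overlap is 21 − *d* days, and none once *d* reaches 21. A 28-day-old test reflects about days 28 to 49, which is before all the qualifying spraying and before any symptom that began in the last four weeks.

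**The case against.** - **Silence is not absence.** A reader might infer that illness is pooled whatever its onset. The article does not say so. The form is not shown and may ask about onset, and the variables to be combined are to be listed in advance. This stands: the point is only that the outcome definitions shown do not use the window.
- **Direction.** A reader might also infer that the association is diluted towards the null by design. That needs earlier illness to be unrelated to current AChE. Participants grow vegetables for sale at least 10 months a year, so current AChE may well track habitual exposure, and then the table shows no dilution. This stands: the direction cannot be fixed from the documents.
- **Composite only.** The arithmetic concerns any ill-health. A separate model for one acute symptom is not contaminated by unrelated chronic disease in this way. This stands, although a single-symptom model still needs a recall period that fits the window.
- **No hard cutoff.** Three weeks is when recovery begins, so it would be too strong to say that earlier illness cannot be related to the exposure detected.
- **Safeguards.** The models are called exploratory, the Limitations warn against reading association as causation, and earlier diagnosed poisoning is excluded in a sensitivity analysis. These help, but the caveat does not address timing, and the exclusion leaves undiagnosed episodes and chronic disease in place.
- **Consequence.** Nothing in the article says a null result would be read as little health impact. That is a risk of misreading, not a stated plan.

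**Conclusion.** The concern holds in a limited form. The article sets a short-window measure against illness outcomes with no stated time frame, although its own background and eligibility reasoning separate recent from long-term effects. The resulting association may be biased, most of all for the composite. On the assumed inputs, a true OR of 2.0 becomes about 1.3 to 1.6 if 10% to 40% report unrelated earlier illness, changes little under habitual exposure, and may pass the null if ill workers have cut back spraying. All illness rates and link strengths are assumptions, so the figures show what is possible and do not estimate this study's bias. The prevalence objective and its precision are untouched. A change is advisable because a result open to all three readings cannot be interpreted, and the remedy is cheap.

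**What to change.** 1. In models with AChE as a predictor, make the main ill-health outcome acute symptoms of the kind listed in Background that were present or began within the AChE window before the blood test. Use the form's onset or recall items, or add one per symptom if there is none.
2. Keep any ill-health, chronic conditions and earlier episodes as secondary outcomes, reported separately, with the caveat that one AChE test cannot address them. AChE need not be dropped from those models. That is a matter of preference.
3. Reconcile the four-week allowance for existing Thai tests with the three-week window, for example by a sensitivity analysis excluding tests taken before the interview. Record the dates of test and interview so that the symptom window can be anchored to the test.
4. Retain the planned exclusion of earlier diagnosed poisoning.

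The cost is fewer events, and so less precision, in the acute-symptom models, and possibly one extra question per symptom in a form that the Timeline wanted final by the end of March 2021. Workers already interviewed without such an item could be classified only by type of symptom.
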